To meet our secondary objective of investigating health service utilisation in multimorbid patients, we will use a retrospective cohort design. We will create a cohort of patients beginning on January 1, 2012 and following these patients over four years until December 31, 2015. The exposed group will be all patients who have multimorbidity as of January 1, 2012, and the unexposed group will be patients who do not have multimorbidity. We will look at the relationship between the exposure of multimorbidity and the outcome of health service utilisation, which will be assessed based on number of GP consultation, number of prescription medications, and number hospital admissions over the four-year follow-up period. This study design will help us account for the effect of differential mortality that may potentially occur between the exposed and unexposed groups. Mortality will be a secondary outcome in our four-year follow-up. Any patients who have transferred out of their practice during the follow-up period will be censored.

1. **Sample Size**

*Please provide an estimate of sample size, and, where possible, a formal power calculation. An estimate of the expected number of patients available in the CPRD database should normally be included.*

For our primary objective of describing the prevalence of multimorbidity, we have calculated a sample size estimate of 425,400 patients.

This sample size calculation was obtained using the following formula for calculating sample size in cross-sectional studies of prevalence^21^.

$$n=\frac{Z^{2}P\left( 1-P \right)}{d^{2}}$$

In this formula, *n* is the sample size and Z is the test statistic corresponding to a 95% confidence level. P is the expected prevalence of multimorbidity. We set P to be 23.2%, which was the prevalence of multimorbidity obtained by the Barnett *et al.* study on a similar population in Scotland^4^. *d* is the precision of the estimate, corresponding to the effect size. We set size *d* to be 0.13%, which was based on the 95% confidence intervals of the prevalence of multimorbidity from the Barnett, *et al* paper^4^*.*

Using the LSOA “Linked Source Data”, we observed that there are currently 95.2% English patients who have patient level IMD data.  We therefore increased our sample size from 405,000 to 425,400 to account patients who will have to be dropped due to missing IMD data.

1. **Data Linkage Required (if applicable)**

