*Please provide a synopsis of the purpose(s) for which the each of the linkages requested in section 18 of the application form is required.*

The proposed linkage of GOLD data to the patient-level Index of Multiple Deprivation (IMD) dataset will enable us to obtain an estimate of socioeconomic status, which we consider a key predictor of multimorbidity^4,5,22^. The proposed linkage to the Integrated Hospital Episode Statistics (HES) datasets will allow us to obtain much more complete ethnicity data^23^, which we believe to be an important predictor of multimorbidity that has not been adequately addressed in the current literature^24^. It will also allow us to obtain information about the number of hospital admissions, which is one of our outcomes for measuring health service utilisation.

1. **Study Population**

*Define the source and study population, in terms of persons, place, time period, and listing the criteria which will be used to select the study population from the CPRD, i.e any inclusion or exclusion criteria. Please make clear any restrictions imposed by the use of linked datasets.*

A random sample without replacement of approximately 425,400 patients taken from all adults 18 years or older who were currently registered with a GP on or before December 31, 2015.

1. **Selection of comparison group(s) or controls**

*Describe the criteria for eligibility and the procedure for control selection.*

For the retrospective cohort component of our study, cases are all patients in the dataset who have multimorbidity, defined as having two or more of the morbidities listed in Appendix A. The comparison control group will consist of patients who either have zero or one current morbidities in their medical record.

1. **Exposures, Outcomes and Covariates**

*For exposures and outcomes operational definitions (or procedures for developing them) must be provided, supported by preliminary code lists placed in an Annex. A comprehensive list of covariates should also be provided for any study which is not purely descriptive.*

*Exposures and Outcomes for Primary Research Objective:*

Since this is a descriptive study, we do not have a specific exposure for our primary objective. However, we will consider several covariates in our analysis including age, sex, ethnicity, socioeconomic status (using IMD deciles), smoking status, and region.

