The outcome of our descriptive analysis is the prevalence of multimorbidity, and we will define multimorbidity using a list of 36 comorbidities (Appendix 1). See Section D for the rationale for choosing these specific morbidities.

In addition to describing the prevalence of multimorbidity, as part of our descriptive analysis we are interested in the pairing and clustering of different comorbidities. To assess the frequency of the most commonly paired comorbidities, our outcome will be pairs of any two separate morbidities from the code list of 36 comorbidities. Additionally, to evaluate our final descriptive outcome relating to the prevalence of physical-mental health comorbidities, mental health comorbidities will be defined as Depression and Anxiety, Alcohol Problems, Dementia, Learning Disability, and Schizophrenia or Bipolar Disorder. All other morbidities will be defined as physical (See Appendix 1).

*Exposures and Outcomes for Secondary Research Objective:*

Our secondary research objective is to investigate the association between multimorbidity and health service utilisation. The exposure for this four-year retrospective cohort study is multimorbidity, which has been defined above.

We will consider three patient-level health service utilisation outcomes:

- the number of GP practice consultations (in-person or by phone)
- the number of prescriptions a patient has been issued
- the number of hospital admissions.

We will consider mortality as a secondary outcome of the retrospective cohort component of our study.

1. **Data/ Statistical Analysis**

*This section should cover both the analytic methods and also the analyses which are to be performed to meet all the specific aims listed earlier. It is important to ensure that this section is clear and specific about any comparisons which will be made*

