To meet our first aim of describing the epidemiology of multimorbidity, we will estimate the prevalence of multimorbidity and explore how this may differ according to patient-level characteristics. We will use a chi-square test to examine differences in presence of multimorbidity (0-1 morbidities versus 2+ morbidities) in relation to sociodemographic characteristics outlined above. We will use a t-test to assess differences in the mean number of morbidities by sex, and one-way ANOVA to test differences in the mean number of morbidities by age (which will be categorised in 10-year age intervals), ethnicity, socioeconomic status (IMD deciles), smoking status, and region.

To meet our second aim of investigating the frequency of pairs of two comorbid conditions, we will describe the prevalence of frequently occurring disease pairs, which we consider to be any pair of comorbidities with a prevalence >5%. These pairs will be identified by calculating the prevalence for all 630 ( $\frac{36*35}{2}$) potential disease couplets, and then reporting the comorbidity pairs with >5% prevalence. As this is a descriptive study, we are primarily interested in identifying the most commonly occurring disease couplets, and describing their prevalence. Clinical appraisal of the most prevalent couplets will be conducted to establish whether these pairs are common because of a causal link, or common because each has relatively high prevalence. These differences will be addressed in our discussion. A chi-squared test will be used to evaluate the association of these co-occurring morbidity pairs (e.g. having the comorbidity pair of interest versus having a different combination of comorbidities) in relation to sociodemographic characteristics. A one-way ANOVA test will be used to assess differences in the mean number of morbidities an individual has given that they have a specific pairing of commonly occurring comorbid diseases.

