To meet our third aim of examining mental morbidities and the linkage of physical and mental comorbidities, we will report the percentage of individuals with both a physical and mental comorbidity. We will use a logistic regression, controlling for sociodemographic characteristics, to quantify the association between mental and physical morbidities, with the binary outcome being the presence of a mental health comorbidity. We will report odds ratios and covariate adjusted odds ratios of having any mental health disorder based on the number of physical morbidities an individual has. We will also report the odds ratios by sociodemographic characteristics. Additionally, we will use a chi-squared test to assess differences between the prevalence of any multimorbidity and the prevalence of having a physical-mental health comorbidity between our sociodemographic covariates described in Section K.

To meet our fourth aim of describing health service utilisation, we will use the total number of consultations as the denominator to evaluate the proportion of consultations devoted to patients with different levels of multimorbidity. We will also use the mean and standard deviation of the number of consultations and prescriptions to describe consultation and prescribing rates in relation to the number of morbidities. We will calculate the total number of consultations, prescriptions, and hospitalisations a patient has during our four-year study period, and will explore the patterns of the data to determine the most appropriate form of regression to look at the separate relationships between the number of morbidities and the number of consultations, prescriptions, and hospitalisations. In this analysis, we will adjust for patients who died during the four-year follow-up as well as for patients who have been censored due as a result of transferring out of the practice. We will use a Cox proportional hazards model to describe the differences in mortality rate between exposed multimorbidity patients and non-multimorbid patients. All regression analyses will consist of a crude analysis in addition to an adjusted one incorporating the covariates described in Section K.

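### The aim 3 chi-squared test sets the prevalence of multimorbidity against that of physical-mental comorbidity, a subset of it, so the literal comparison breaks the test's independence assumption

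*Protocol*

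**What the plan says.** The Data/Statistical Analysis section, third aim, plans three things.

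- A percentage: "we will report the percentage of individuals with both a physical and mental comorbidity".
- A logistic regression, crude and adjusted, with presence of any mental health comorbidity as the outcome and the number of physical morbidities as the exposure.
- A further test: "we will use a chi-squared test to assess differences between the prevalence of any multimorbidity and the prevalence of having a physical-mental health comorbidity", a sentence that goes on "between our sociodemographic covariates described in Section K".

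The definitions stand elsewhere. Under Selection of comparison group(s) or controls, multimorbidity is "defined as having two or more of the morbidities listed in Appendix A". Under Exposures, Outcomes and Covariates, "mental health comorbidities will be defined as Depression and Anxiety, Alcohol Problems, Dementia, Learning Disability, and Schizophrenia or Bipolar Disorder", and then "All other morbidities will be defined as physical (See Appendix 1". For the first aim, a chi-square test will already "examine differences in presence of multimorbidity (0-1 morbidities versus 2+ morbidities) in relation to sociodemographic characteristics". None of the four amendments changes the third-aim sentence.

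**The concern.** A Pearson chi-squared test assumes that each patient falls in one cell of the table. The two quantities named in the sentence do not allow that. A patient with at least one physical and at least one mental condition has at least two conditions, so the physical-mental group lies wholly inside the multimorbid group.

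At stake is whether mixed physical-mental disease is spread across age, sex, ethnicity, deprivation, smoking and region in the same way as multimorbidity in general. Taken literally, the planned test either reports a difference that the definitions impose, or uses a variance that is too large and so tends to miss real differences.

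**Working it through.** **Inputs from the protocol.** Expected multimorbidity P = 23.2%, d = 0.13%, 95% confidence, 95.2% of patients with IMD data (Sample Size); 36 conditions, of which 5 are mental and 31 physical (Exposures, Outcomes and Covariates; Appendix 1); IMD in deciles.

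**Assumptions not in the protocol.** q, the share of multimorbid patients who are physical-mental, at 20%, 36% and 50%; equal-sized deciles; and, for the decile scenario, multimorbidity rising evenly from 20% to 26.4% (mean 23.2%).

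**1. The plan's own figure.** n = 1.96² × 0.232 × 0.768 / 0.0013² = 405,018 (405,003 with unrounded Z), against 405,000 stated. 405,000 / 0.952 = 425,421, against 425,400 stated. Both reproduce. They only set the scale here: ten deciles of 40,500, or two groups of 202,500.

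**2. Nesting.** At least 1 physical + at least 1 mental = at least 2 conditions. In 200,000 simulated patients over 36 conditions (5 mental, 31 physical), none was physical-mental without being multimorbid.

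**3. Direct comparison of the two prevalences.** The difference is P − qP = P(1−q), the prevalence of other multimorbidity, which can never be negative. In one decile (n = 40,500), z = (P − qP) / √(2 p̄(1−p̄)/n), with p̄ = (P + qP)/2. For q = 36%: p̄ = 0.1578, SE = 0.00256, z = 0.1485/0.00256 = 58. For q = 20% and 50%, z = 76 and 44. Rejection says nothing about sociodemographic pattern.

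**4. Overlapping counts stacked as two rows across groups.** With M multimorbid and qM physical-mental patients in a group:

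- variance of the log ratio assumed by the test: 1/(qM) + 1/M = (1+q)/(qM);
- actual variance, since the second count is drawn from the first: (1−q)/(qM).

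The statistic is therefore shrunk by (1−q)/(1+q). Simulation with two groups of 202,500, multimorbidity 23.2% in both, 20,000 runs, nominal 5%:

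| q | Factor | Level, stacked | Level, disjoint | Power, stacked | Power, disjoint |
|---|---|---|---|---|---|
| 20% | 0.67 | 1.7% | 5.0% | 92% | 97% |
| 36% | 0.47 | 0.4% | 4.7% | 62% | 89% |
| 50% | 0.33 | 0.1% | 5.3% | 36% | 87% |

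Power is for a 1-point difference in q between the groups. Disjoint means physical-mental versus other multimorbidity.

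Over ten deciles with the assumed gradient and q constant, the stacked test rejects in 0.4% of runs or fewer. If q rises by 2 points across deciles, its power is about 73%, 13% and 0.6% for q = 20%, 36% and 50%, against about 95%, 82% and 79% for the disjoint test.

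**5. Separate yes/no tests of each prevalence by group.** Each patient is counted once, so the level is right: 4.8% to 5.1% when prevalence is the same in both groups. The question is a different one, as two decile scenarios show:

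- q constant, multimorbidity rising: the physical-mental test rejects in 100% of runs, correctly, because that prevalence does rise. The disjoint test rejects in about 5%, because the share does not change.
- q falling as multimorbidity rises (41.8% to 31.6% in the middle case), so that physical-mental prevalence is flat: the physical-mental test rejects in 4% to 5%, the disjoint test in 100%.

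**The case against.** The strongest answer rests on the end of the sentence, "between our sociodemographic covariates described in Section K". With the first-aim analysis as a model, it can be read as two separate tests, one per prevalence, each across sociodemographic groups. Nesting does not matter in either table. This reading is possible, and the tests are valid for their own null hypotheses. It sits poorly with the words, though: the first aim already tests multimorbidity by the same characteristics, and the sentence speaks of differences between the two prevalences.

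A reader might infer that no version of the test has a correct error rate, or that the plan cannot answer the question at all. The documents do not support that. Separate tests hold their level, and their rejection under a real gradient is true detection, not error. The stacked table is conservative, yet still responds to differences, with 73% power in the decile scenario at q = 20%. Nor does the protocol say that overlapping counts would be stacked.

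It may also be said that the layout of a table belongs in a statistical analysis plan. That would hold had the protocol been silent. It names both the test and the two quantities compared, and those quantities are nested. For disease pairs in the second aim it does state a disjoint contrast: the pair of interest against a different combination.

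It stands that this is a supplementary test in a mainly descriptive study, and that the reported percentage and the planned odds ratios do not depend on it.

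**Conclusion.** The point holds in a limited form. By the protocol's own definitions the sentence compares a group with its own subset. Taken literally, that gives either a certain rejection or, if stacked, a statistic reduced to roughly one third to two thirds of its proper size for q between 50% and 20%. The lenient reading is valid but leaves untested whether the two are distributed differently.

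The nesting and the factor (1−q)/(1+q) follow from the definitions and algebra. The rejection and power figures depend on q, equal-sized groups and, for the deciles, a gradient, none of which the protocol gives. The planned logistic regression neither suffers from the problem nor repairs it: its outcome is any mental disorder, which includes patients with one mental condition and no multimorbidity. The wording should be corrected, but the main results of aim 3 are not in doubt.

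**What to change.** Replace the chi-squared sentence under the third aim with two tests:

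1. In the whole sample, a chi-squared test of physical-mental comorbidity (yes/no) across each sociodemographic characteristic. This keeps the population prevalence that the protocol names as its outcome.
2. Among patients with two or more morbidities, a chi-squared test of physical-mental versus other multimorbidity across the same characteristics. These groups do not overlap, and the test addresses directly whether the share differs.

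If an adjusted version of the second test is wanted, specify a logistic model among multimorbid patients with physical-mental status as the outcome. The model already planned cannot serve, because its outcome is different.

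The cost is a rewritten sentence and one extra table or model, from the same data. The second result describes a share among multimorbid patients, not a population prevalence, and should be labelled so.

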**Amendment 2**

The following amendment is proposed, as of 24/09/2018:

Investigators

The research team would like to add statisticians [name], [name], [name] and [name] to the project.

Objectives

We wish to update Objective 5:

1. To determine patterns of multimorbidity disease combinations associated with health service utilisation outcomes, treatment burden, mortality, index of multiple deprivation and age in order to identify clusters of patients that are in some respect “similar.”

Data Linkage Required (if applicable)

To assess the relationship between multimorbidity clusters and mortality, we additionally wish to link ONS mortality data.

Data/Statistical Analysis

We propose to use profile regression (see below) instead of latent class analysis to cluster patients based on their health conditions. Formally, profile regression is a latent class analysis, with the addition that clusters are sought which are related to the outcome. As described above, we will generate clusters associated with health service usage, treatment burden (number of current prescription medications), mortality, index of multiple deprivation and age. This will ensure the clusters found are relevant to those outcomes, and so will be most useful. Rather than random effects for practices, we will study the impact of practice-level variation by adding it as a fixed effect co-variate into our model. We will perform cross-validation to ensure the robustness of our results.

**Reference for profile regression:** https://arxiv.org/abs/1303.2836

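### Aim 4 reports consultation and prescribing rates as mean counts with no person-time denominator, although death and transfer make follow-up unequal

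*Protocol*

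**What the plan says.** Under Objectives, Specific Aims and Rationale, aim 4 speaks of GP consultations and prescriptions per year, together with hospital admissions.

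Under Data/Statistical Analysis, the descriptive part of that aim uses the "mean and standard deviation of the number of consultations and prescriptions to describe consultation and prescribing rates", broken down by number of morbidities. The next sentence reads: "We will calculate the total number of consultations, prescriptions, and hospitalisations a patient has during our four-year study period". It goes on to leave the form of regression open until the data have been explored. After that comes: "In this analysis, we will adjust for patients who died during the four-year follow-up as well as for patients who have been censored" because they left the practice. No method of adjustment is given.

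Under Study Design, the cohort starts on 1 January 2012, "following these patients over four years until December 31, 2015". On leaving the practice, the rule is: "Any patients who have transferred out of their practice during the follow-up period will be censored". The design is said to help "account for the effect of differential mortality that may potentially occur between the exposed and unexposed groups".

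The protocol gives no death rate, transfer rate or expected level of service use, either overall or by number of morbidities.

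**The concern.** A mean count equals a rate only when everyone is observed for the same time. Here the protocol itself says they will not be: patients leave observation at death and at transfer, and mortality may differ between the exposure groups. A patient who leaves after one year adds one year of events to a mean that will be read as covering four. Dividing that mean by four then gives too low an annual figure. How much too low depends on how quickly patients in that morbidity group leave observation.

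The shortfall therefore varies along the exposure, so both the level of use in each group and the comparison between groups are affected. A reader of the published means could not correct them without knowing the follow-up time per group. Describing service use in relation to multimorbidity is the protocol's secondary objective.

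**Working it through.** The protocol states no figure for aim 4 that could be reproduced. The calculation below shows only how far unequal follow-up can move the results.

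**Inputs**
- Follow-up window T = 4 years (Study Design).
- Ways of leaving early: death and transfer out (Study Design; Data/Statistical Analysis).
- Annual hazards of death and transfer: assumed, because the protocol has none.
- Use while registered: assumed constant at 3 events per year in the less multimorbid group and 9 in the more multimorbid group, a true ratio of 3.00. The percentage shift in the ratio does not depend on these two values.

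**Formulas**
- Total exit hazard h = death hazard + transfer hazard.
- Expected person-years PY = (1 - exp(-hT)) / h.
- Four-year mean divided by 4 = true annual rate × PY / 4.
- Ratio of raw means = true ratio × PY(more) / PY(less).

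**Step 1: level of the annualised mean**

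| h per year | PY | PY / 4 | Understatement |
|---|---|---|---|
| 0.005 | 3.960 | 0.990 | 1% |
| 0.03 | 3.769 | 0.942 | 6% |
| 0.05 | 3.625 | 0.906 | 9% |
| 0.08 | 3.423 | 0.856 | 14% |
| 0.10 | 3.297 | 0.824 | 18% |

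For example, at h = 0.10: (1 - exp(-0.40)) / 0.10 = 3.297, and 3.297 / 4 = 0.824.

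**Step 2: ratio between groups (less versus more multimorbid)**

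| Death hazard | Transfer hazard | PY | Raw ratio (true 3.00) | Shift |
|---|---|---|---|---|
| 0.003 vs 0.03 | none | 3.98 vs 3.77 | 2.84 | -5% |
| 0.005 vs 0.10 | none | 3.96 vs 3.30 | 2.50 | -17% |
| 0.005 vs 0.03 | 0.05 vs 0.05 | 3.59 vs 3.42 | 2.86 | -5% |
| 0.003 vs 0.10 | 0.08 vs 0.03 | 3.40 vs 3.12 | 2.75 | -8% |
| 0.003 vs 0.03 | 0.07 vs 0.043 | 3.47 vs 3.47 | 3.00 | 0% |
| 0.005 vs 0.03 | 0.08 vs 0.03 | 3.39 vs 3.56 | 3.15 | +5% |

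Where loss through death dominates and is greater in the more multimorbid group, the ratio is pulled down. Where the less multimorbid transfer out more often, the two losses can cancel or the ratio can be pushed up.

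**Step 3: if counts are taken year by year**

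The aim's per-year wording permits this reading. With T = 1, PY at h = 0.10 is (1 - exp(-0.10)) / 0.10 = 0.952, a shortfall of about 5% among patients still registered at the start of the year. At h = 0.005 it is 0.9975, or about 0.3%. The shortfall is smaller but does not vanish, and a denominator is still needed.

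**Step 4: with person-time**

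Under the same assumptions, total events divided by total person-years returns 3 and 9 per year, ratio 3.00, in every row.

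**The case against.** The best defence is that the protocol has not overlooked death and transfer. It names differential mortality, says it will adjust for both, and leaves the form of regression open. An offset is the kind of detail a separate analysis plan may settle. The descriptive sentence does not itself mention four years, and the aim's per-year wording points to annual figures. The phrase introducing the adjustment could also be read as covering the whole of aim 4.

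Much of this stands, and it limits the point. That the means are of four-year totals is an inference from the neighbouring sentence. But the adjustment sentence follows the regression and most naturally belongs to it. For the descriptive part the protocol is not silent: it names a statistic, and that statistic is not a rate when follow-up differs.

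Three stronger readings are tempting and are not supported:

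- *The gradient is necessarily flattened.* This needs loss through death to dominate and to rise with the number of morbidities. The protocol gives no rates, and the scenarios above include no shift and a steeper gradient. Heavier use shortly before death, which the constant-use model ignores, would also offset part of the loss.
- *"we will adjust for patients who died during the four-year follow-up" means a covariate for death.* Such a term would condition on a later event that is itself a study outcome, and it would not correct time at risk. But the words are equally open to an adjustment for follow-up time. The text needs clarifying; it is not a shown error.
- *Censoring admissions and deaths at transfer is wrong because they come from linked data.* The application form warns that linked data do not cover all patients and that coverage periods differ. Amendment 2 says "we additionally wish to link ONS mortality data" in order to relate multimorbidity clusters to mortality, not for aim 4. One censoring rule also gives all outcomes the same risk window and fits the planned adjustment for clustering by practice. This is a defensible trade-off.

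**Conclusion.** The point holds for the descriptive part of aim 4: what it calls rates are mean counts without a person-time denominator, in a cohort whose follow-up the protocol knows to be unequal. On the four-year reading, annualised levels would be understated by about 1% to 18% at total exit hazards of 0.005 to 0.10 per year. Between two groups the ratio would shift by about -17% to +5% over the scenarios tried. These sizes rest on assumed constant hazards and constant use while registered; they illustrate the sensitivity and do not estimate the bias in this cohort. The sign of the effect on the gradient cannot be settled from the protocol.

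The regression is affected only in that the meaning of its adjustment is left open. The primary objective, prevalence, is untouched. So is the planned share of all consultations taken by each morbidity level, which describes workload and needs no person-time.

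**What to change.** In the aim 4 text of Data/Statistical Analysis:

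1. Replace the mean and SD as the description of rates by total events divided by total person-years at risk, by number of morbidities, with 95% confidence intervals. Do this for consultations, prescriptions and admissions, with follow-up ending at the earliest of death, transfer out and 31 December 2015. Mean counts may stay if they are labelled as counts over observed follow-up and shown beside the person-years.
2. State that the regression's adjustment for death and transfer means log(follow-up time) as an offset in the chosen count model, with no covariate for later death.
3. Keep censoring at transfer as the main rule. If linked coverage after transfer is confirmed, following admissions and deaths beyond transfer could be offered as a sensitivity analysis.

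The cost is a few lines of text and code. The dates of death and transfer are already needed for the planned censoring and the mortality model, so items 1 and 2 call for no new data.
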